### Blinding

Blinding of healthcare professionals is not feasible due to the distinct visual differences between propofol (a white lipid emulsion) and ketamine (colorless). However, data collectors, outcome assessors, and statisticians will remain blinded to group allocation to minimize bias.

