### Randomization and concealment

Patients will be randomized to receive either ketamine or propofol via a central, web-based, automated randomization system (RedCap UNIFESP), accessible 24 hours per day. An external individual not involved in the study will generate a list using the randomization tool on random.org. Patients will be randomized in a 1:1 ratio, in blocks of variable size, stratified according to study site and use of vasopressors. The central automated system will maintain the confidentiality of the randomization sequence. Site investigators will be unaware of the block sizes, ensuring adequate concealment of the randomization sequence. The system will allow only one randomization per patient, and study team members at each site will be responsible for enrolling patients and assigning interventions. The flowchart is available in figure 1S (Supplementary Material).

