If the first attempt is unsuccessful, the patient will be reoxygenated before another attempt is made. If intubation remains unsuccessful after two attempts, a qualified alternate operator or adjunct devices will be utilized. If additional medications are required, the study hypnotic agent will be used, with dosing at the discretion of the attending team. All intubation steps will follow a strict protocol, and patients will undergo an intubation checklist as per routine in the participating units (Figure 2S - Supplementary Material). Continuous monitoring will be performed using electrocardiography, pulse oximetry, and invasive or non-invasive blood pressure monitoring. The monitor will proceed with measurements every 2 minutes for patients with noninvasive blood pressure measurement. The use of vasoactive drugs before induction will be initiated only if the patient's mean arterial pressure (MAP) is below 65mmHg, following the institutional protocol. Doses of vasoactive drugs can be adjusted during the procedure at the discretion of the ICU team. In both groups, general management, such as pre-oxygenation, ventilatory support, and use of adjunctive devices, will follow the ICU protocol (Supplementary Material). Data on adherence to the study protocol, including successful medication administration, will be collected for all patients who undergo intubation in both groups. Any instances patients do not receive the assigned medication will be documented, including the reason for non-administration.

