### Outcomes

The study's primary outcome is the lowest MAP recorded within the first 10 minutes following the induction for intubation.

Secondary outcomes include:

–Average MAP within the first hour after induction.–Mortality within the first hour after induction.–Cardiac arrest within the first hour after induction.–Occurrence of severe hypotension, defined as systolic blood pressure (SBP) < 80mmHg, within 1 hour after induction.–Occurrence of severe hypoxemia, defined as peripheral oxygen saturation (SpO_2_) < 85%, within one hour after induction.–Time for successful intubation.

Tertiary outcomes include:

–The number of intubation attempts.–The highest HR within 1 hour after induction.–The total dose of vasopressors administered within the first 24 hours, using the noradrenaline equivalent dose.–Mean change in vasopressor dose (norepinephrine equivalent) from baseline to hour 1.–Ventilator-free days within the first 7 days, defined as the number of days on which individuals are able to breathe spontaneously without any invasive ventilatory assistance, ascribing zero days to those who die within 7 days.–Mortality at day 7.–ICU mortality.–Hospital mortality.

Safety outcomes will be assessed during the first 10 minutes following induction, and will include:

–Hypertension, defined as SBP > 180mmHg.–Laryngospasm, as reported by the physician in charge of intubation.–Bradycardia, defined as HR < 45 bpm.–Arrhythmias.–Bronchoaspiration, defined as the presence of gastric content aspirated into the airway during intubation.

All outcome data will be presented as specified on the electronic supplemental materials (Table 1S - Supplementary Material). The trial sequence is available in figure 1.

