### Data collection

Demographic characteristics, comorbidities, clinical data, and severity of illness will be collected at baseline for all patients (Table 2S - Supplementary Material). Additional data on the procedure characteristics will also be collected (Table 3S - Supplementary Material). During and after the procedure, hemodynamic data will be registered at the following time points: 1 minute before induction; every 2 minutes during the first 10 minutes after the administration of the study medication; every 5 minutes up to one hour after induction (Table 4S - Supplementary Material). Doses of vasoactive drugs will also be recorded. Any adverse events occurring within the first hour post-induction, including death, cardiac arrest, arrhythmias, bronchoaspiration, and laryngospasm, will be documented.

Patients will be followed until hospital discharge, censored at day 60^th^, to determine the need for mechanical ventilation up to day 7, vital status at day 7, in the ICU, and in the hospital. Patients who are withdrawn from the study for safety reasons (excluding those who withdraw consent) will be included in the analysis on an intention-to-treat basis.

Data will be collected via electronic forms using the RedCap platform and securely stored. The investigators will complete the forms, using specific passwords for access. Training will be provided for all personnel involved in the study to ensure high-quality data collection. The principal investigator will be available to answer any questions regarding form completion. Data consistency will be periodically reviewed, and any discrepancies will be addressed by contacting the sites for clarification and correction.

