## DISCUSSION

This study protocol outlines a randomized, open-label, pragmatic, bicentric trial designed to evaluate the effects of ketamine versus propofol as the hypnotic agent in critically ill patients undergoing RSI. The primary outcome of the study is the lowest MAP within 10 minutes after induction for intubation. Secondary outcomes include various cardiovascular and respiratory parameters, adverse events, and patient-related outcomes such as ventilator-free days and mortality.

The findings from this study could provide important insights into the comparative efficacy and safety of two commonly used anesthetic agents in a high-risk ICU setting and have the potential to significantly influence clinical practice. If ketamine is shown to be superior to propofol in maintaining hemodynamic stability without compromising sedation quality, it may become the preferred choice for intubation in this patient population. On the other hand, if propofol is found to be equally effective but with fewer adverse events or a more favorable safety profile, it could continue to be a viable option in certain circumstances.

Our study design has several strengths. The study will be conducted in two ICUs serving a diverse population of high-complexity medical and surgical patients. Additionally, using randomization with concealment of allocation through a centralized, web-based system helps minimize selection bias. Our predefined primary and secondary outcomes are clinically relevant and directly tied to patient safety and treatment efficacy. Furthermore, the protocol incorporates a well-defined safety monitoring framework, with an independent DSMB overseeing the study's progress and ensuring the safety of participants.

There are also several limitations. The open-label design may introduce performance bias. Although blinding is not possible for the healthcare providers administering the medications, efforts to blind outcome assessors, data collectors, and statisticians will help minimize bias in outcome assessment.

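### Blinding of data collectors and outcome assessors is claimed without exception, but the article contradicts it for three items and does not show it workable for the primary outcome

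*Protocol article*

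**What the plan says.** The Blinding section concedes that healthcare professionals will know the drug, since propofol is a white emulsion and ketamine is clear. It then states that "data collectors, outcome assessors, and statisticians will remain blinded to group allocation to minimize bias". No outcome or role is excepted. The Discussion admits possible performance bias from the open-label design and relies on this safeguard: "efforts to blind outcome assessors, data collectors, and statisticians will help minimize bias in outcome assessment".

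Other sections describe who does what:

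- Outcomes, safety list: "Laryngospasm, as reported by the physician in charge of intubation".
- Interventions, on adherence: "Any instances patients do not receive the assigned medication will be documented, including the reason for non-administration".
- Safety and adverse events: whether a complication counts as an adverse event depends in part on whether the attending physician considers it unexpected. Serious events are adjudicated by physicians outside the study team; whether these are blinded is not stated.
- Data collection: hemodynamic values are registered "every 2 minutes during the first 10 minutes after the administration of the study medication", and "The investigators will complete the forms, using specific passwords for access".
- Randomization and concealment: "study team members at each site will be responsible for enrolling patients and assigning interventions".

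**The concern.** An unqualified blinding claim is hard to square with an open-label drug comparison in which some events are reported by the operator. Readers will judge the risk of detection bias from the Blinding section, and the Discussion invites them to. If some assessors know the arm, the trial would report a protection that it does not have for those items.

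Judgment-based events are the most exposed. The statistical analysis section compares adverse-event frequencies between the arms by chi-squared test, so classification by a physician who knows the arm feeds directly into a between-arm comparison. The primary outcome is exposed in a different way. It is a single minimum, so one repeated cuff reading, or one value set aside as artefact, can change a patient's result if the recorder has discretion and knows the drug.

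**Working it through.** No arithmetic applies, since the article attaches no figure to blinding. The check sets the sections side by side, item by item.

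1. **Laryngospasm.** The assessor is the physician in charge of intubation. That physician is a healthcare professional, a group that the Blinding section itself says cannot be blinded. The claim that outcome assessors are blinded is therefore false for this listed safety outcome. No inference is needed.

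2. **Adherence.** For every intubated patient, the data must show whether the assigned drug was given and, if not, why. A clerk could transcribe a yes or no, but whoever establishes the answer has to know the assignment. At least one person collecting trial data is therefore unblinded. These data also define the per-protocol population.

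3. **Adverse-event classification.** It rests partly on the attending physician, who is again unblinded by the article's own statement. Independent adjudication is described only for serious events.

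4. **Lowest MAP within 10 minutes.** Four statements bear on this:
   - the drugs can be told apart by eye;
   - readings are timed from the study drug;
   - investigators complete the forms;
   - site team members assign treatment.

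   No section separates the person who assigns treatment from the person who records blood pressure. But no section says that they are the same person, that recording is done live at the bedside, or that the recorder sees the syringe. The claim of blinding is unsupported here, not disproved.

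5. **Statistician.** Nothing contradicts blinding. The interim review is unblinded, but it belongs to the independent monitoring board.

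6. **Follow-up outcomes (day 7, ICU, hospital).** Nothing contradicts blinding, provided that the person collecting them has no access to the allocation.

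The result is three items contradicted, one not shown to be workable, and the rest uncontradicted.

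**The case against.** The strongest reply is that this is a condensed article. Who records blood pressure, and on which form, is operational detail that may sit in the full protocol or in the supplementary tables, which are separate for procedure characteristics and for hemodynamic data. The investigators who complete forms need not be the team members who assign treatment. In patients with cuff measurement the monitor cycles every 2 minutes, and registration times are fixed, so discretion is limited. MAP and mortality are not judgment-based. The Discussion speaks only of efforts that help to reduce bias.

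Most of this stands for the primary outcome. A reader might infer that the people recording MAP see the drug, so that the primary outcome is assessed unblinded. The documents do not establish that. A reader might also conclude that the whole safeguard is absent. That goes too far, because blinding of the statistician is uncontradicted and serious adverse events go to independent adjudicators. Nor can a bias in mmHg be stated: it would need a rate of discarded readings, a gap between the lowest and next-lowest value, and a degree of imbalance between arms, none of which the article gives.

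The reply does not reach the three contradicted items. No supplement can blind the operator who reports laryngospasm or the attending physician who judges an event, or let adherence be established without knowing the assignment.

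**Conclusion.** The point holds in limited form. The statement that data collectors and outcome assessors are blinded is wrong for operator-reported laryngospasm, for adherence data and for adverse-event classification by the attending physician. Confidence in this is high, since it rests on the article's own text.

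For peri-induction MAP, the article does not show how blinding would be achieved. Confidence that it would fail is only moderate, because this assumes that recorder and treating team are not separated, which the article neither says nor excludes.

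The consequence is for what the trial may claim about detection bias. No effect on the treatment estimate can be sized from the documents. The change should be made, because the Discussion relies on the claim and correcting it costs little.

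**What to change.** 1. **Restate the claim in the Blinding and Discussion sections.** Claim blinding for the statistician and for outcomes recorded by someone without access to the allocation. Name who records each outcome. Describe laryngospasm, adherence and adverse events judged by the attending physician as open-label assessments.

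2. **Protect the primary outcome where possible.** Where the monitor's time-stamped readings can be retrieved, have the MAP values at the already scheduled points (every 2 minutes to 10 minutes) taken from them by someone without sight of the arm. Apply one artefact rule to both arms, and use a form separate from the drug and adherence fields. Do not take the minimum over the full arterial trend. The schedule gives about five readings (10 / 2 = 5), and a continuous trace gives many more, so the outcome would be redefined in arterial-line patients only and would tend to be lower there.

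**Cost.** Two sections are reworded and some retrieval work is added. The article does not say whether monitor logs are kept; where none exists, the manually recorded value is used and flagged. The stated protection against bias becomes less favorable, but accurate. The outcome definition, the sample size and the analysis model do not change.

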### Interventions

Patients who meet the eligibility criteria will be randomized into one of two groups. Immediately following randomization, during RSI, patients in the intervention group will receive ketamine as the hypnotic agent at a dose of 2mg/kg. Patients in the control group will receive propofol at a 1.5mg/kg dose. Doses will be calculated based on the patient's weight as provided by the attending medical team.

In both groups, premedication will follow the unit's routine protocol, using either 2% lidocaine without a vasoconstrictor at a dose of 1.5mg/kg or fentanyl at 1µg/kg. All patients will receive rocuronium as a 1.2mg/kg dose of neuromuscular blocker.

The drug administration sequence will be identical in both groups. The first drug administered will be either 2% lidocaine (without vasoconstrictor) or fentanyl. After 1 minute, the induction agent (propofol or ketamine) will be administered in a bolus, followed immediately by rocuronium. The infusion rate of the drugs will not be formally specified, but sites will be oriented to follow local guidance for bolus, which will probably result in 10-second administration. Laryngoscopy will be performed 1 minute after neuromuscular blocker administration.

If the first attempt is unsuccessful, the patient will be reoxygenated before another attempt is made. If intubation remains unsuccessful after two attempts, a qualified alternate operator or adjunct devices will be utilized. If additional medications are required, the study hypnotic agent will be used, with dosing at the discretion of the attending team. All intubation steps will follow a strict protocol, and patients will undergo an intubation checklist as per routine in the participating units (Figure 2S - Supplementary Material). Continuous monitoring will be performed using electrocardiography, pulse oximetry, and invasive or non-invasive blood pressure monitoring. The monitor will proceed with measurements every 2 minutes for patients with noninvasive blood pressure measurement. The use of vasoactive drugs before induction will be initiated only if the patient's mean arterial pressure (MAP) is below 65mmHg, following the institutional protocol. Doses of vasoactive drugs can be adjusted during the procedure at the discretion of the ICU team. In both groups, general management, such as pre-oxygenation, ventilatory support, and use of adjunctive devices, will follow the ICU protocol (Supplementary Material). Data on adherence to the study protocol, including successful medication administration, will be collected for all patients who undergo intubation in both groups. Any instances patients do not receive the assigned medication will be documented, including the reason for non-administration.

### Outcomes

The study's primary outcome is the lowest MAP recorded within the first 10 minutes following the induction for intubation.

Secondary outcomes include:

–Average MAP within the first hour after induction.–Mortality within the first hour after induction.–Cardiac arrest within the first hour after induction.–Occurrence of severe hypotension, defined as systolic blood pressure (SBP) < 80mmHg, within 1 hour after induction.–Occurrence of severe hypoxemia, defined as peripheral oxygen saturation (SpO_2_) < 85%, within one hour after induction.–Time for successful intubation.

Tertiary outcomes include:

–The number of intubation attempts.–The highest HR within 1 hour after induction.–The total dose of vasopressors administered within the first 24 hours, using the noradrenaline equivalent dose.–Mean change in vasopressor dose (norepinephrine equivalent) from baseline to hour 1.–Ventilator-free days within the first 7 days, defined as the number of days on which individuals are able to breathe spontaneously without any invasive ventilatory assistance, ascribing zero days to those who die within 7 days.–Mortality at day 7.–ICU mortality.–Hospital mortality.

Safety outcomes will be assessed during the first 10 minutes following induction, and will include:

–Hypertension, defined as SBP > 180mmHg.–Laryngospasm, as reported by the physician in charge of intubation.–Bradycardia, defined as HR < 45 bpm.–Arrhythmias.–Bronchoaspiration, defined as the presence of gastric content aspirated into the airway during intubation.

All outcome data will be presented as specified on the electronic supplemental materials (Table 1S - Supplementary Material). The trial sequence is available in figure 1.

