#### Statistical analysis

Our primary analysis will follow a modified intention-to-treat (mITT) approach. As clinical management might change after randomization, we expect that some patients who will be randomized will not be intubated. Similarly, as we will use a deferred (opt-out) consent process, some patients (or representatives) might not consent. Thus, our mITT analysis will include only those patients who will be intubated and who consent to participate. The data analysis will be performed after submitting the protocol paper and analysis plan for publication.

Categorical variables will be expressed as counts and percentages. Continuous variables will be presented as means and standard deviations (SD) or medians with interquartile ranges (IQR, 25th -75th percentile) as appropriate. For all outcomes, including the primary outcome, we will not impute missing data, and the number of missing values will be clearly presented in tables. Treatment adherence will be reported as each group's mean (SD) number of successful medication administrations.

The primary outcome (lowest MAP within the first 10 minutes post-induction) will be analyzed using a linear regression model, adjusted for baseline MAP before induction, total vasopressor dose in the first 10 minutes, age, and a random patient intercept. A MAP value of 10mmHg (the average cardiovascular filling pressure) will be considered in patients with cardiac arrest.^(14)^ Other vasopressors will be converted to noradrenaline dose equivalents. A per-protocol analysis will be performed, including only patients who received the assigned medication. Additionally, we conducted sensitivity analysis considering the lowest measured blood pressure before cardiac arrest and an unadjusted analysis. In all primary outcome analyses, the effect estimate will be expressed by the mean difference with 95% confidence intervals (95%CI) and p values reported.

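### As the text stands, the 10 mmHg arrest value is tied to the primary outcome, so a fatal first-hour arrest would leave average MAP resting on pre-arrest readings

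*Protocol article*

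**What the plan says.** The secondary outcomes (Outcomes) begin with "Average MAP within the first hour after induction". The same list includes "Mortality within the first hour after induction" and cardiac arrest over the same hour, so the investigators allow for both events in the window being averaged. Severe hypotension over that hour is defined only by a systolic pressure below 80 mmHg.

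The Data collection section schedules pressures "every 2 minutes during the first 10 minutes after the administration of the study medication" and then "every 5 minutes up to one hour after induction".

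The Statistical analysis section contains three relevant statements:
- On missing data: "For all outcomes, including the primary outcome, we will not impute missing data".
- On arrest: "A MAP value of 10mmHg (the average cardiovascular filling pressure) will be considered in patients with cardiac arrest". This stands in a paragraph that opens "The primary outcome (lowest MAP within the first 10 minutes post-induction) will be analyzed using a linear regression model" and ends "In all primary outcome analyses, the effect estimate will be expressed by the mean difference with 95% confidence intervals". The sensitivity analysis using the lowest pressure before arrest is in the same paragraph.
- On secondary outcomes: the only rule for death is zero days for ventilator-free days, and there is no covariate adjustment.

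**The concern.** An average over a fixed hour needs a rule for the part of the hour in which the patient has no circulation. The plan supplies such a rule for the lowest MAP and, separately, a death rule for ventilator-free days. It supplies none for average MAP. Without one, the average is conditional on having a measurable pressure, and the worst minutes of the worst patients drop out.

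The same arrest within 10 minutes would then score 10 mmHg on the primary outcome and leave no trace, apart from any low pressures before it, in the first-listed secondary outcome. If early deaths were unequal between arms, the comparison of average MAP would be shifted in favour of the arm with more of them, in a trial whose question is haemodynamic safety. The two pressure outcomes could disagree merely because they treat arrest differently.

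Severe hypotension has a narrower version of the same gap. A patient who arrests without any recorded systolic pressure below 80 mmHg would not meet the definition.

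**Working it through.** **The plan's own figure.** The sample size uses a 10 mmHg difference, SD 20 mmHg, two-sided alpha 0.05 and 90% power. Per arm, n = 2 × (1.960 + 1.282)² × 20² / 10² = 84.1, rounded up to 85, or 170 in total. The stated 170 reproduces, and this point does not touch it. It supplies the 85 per arm used below.

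**Readings.** From Data collection: 2, 4, 6, 8 and 10 minutes (5 readings), then 15 to 60 minutes in steps of 5 (10 readings), 15 in all after induction.

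**One patient, example A.** Assumed: MAP 65, 55 and 45 at 2, 4 and 6 minutes, then a fatal arrest before the 8-minute reading is obtained.
- Available readings only: (65 + 55 + 45) / 3 = 55 mmHg.
- With 10 mmHg at the other 12 times: (165 + 12 × 10) / 15 = 285 / 15 = 19 mmHg.
- Gap: 55 − 19 = 36 mmHg.

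**One patient, example B.** Assumed: MAP constant at 60, fatal arrest just after the 10-minute reading.
- Available readings only: 60 mmHg.
- With 10 mmHg at the other 10 times: (5 × 60 + 10 × 10) / 15 = 26.7 mmHg. Gap 33.3 mmHg.
- Weighted by time instead: (10 × 60 + 50 × 10) / 60 = 18.3 mmHg. Gap 41.7 mmHg.

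**Range.** Simple mean, constant pre-arrest MAP of 50 to 70 mmHg, arrest between 5 and 41 minutes (all assumed):
- Smallest gap (MAP 50, arrest at 41 minutes, 11 readings before it): 50 − (11 × 50 + 4 × 10) / 15 = 50 − 39.3 = 10.7 mmHg.
- Largest gap (MAP 70, arrest at 5 minutes, 2 readings before it): 70 − (2 × 70 + 13 × 10) / 15 = 70 − 18.0 = 52.0 mmHg.

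**Arm mean.** Shift per such patient = gap / 85.
- Example A: 36 / 85 = 0.42 mmHg.
- Example B: 33.3 / 85 = 0.39 mmHg.
- Range: 10.7 / 85 = 0.13 to 52.0 / 85 = 0.61 mmHg.

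An excess of one to five example A patients in one arm shifts the between-arm difference by 0.42 to 5 × 36 / 85 = 2.1 mmHg.

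**Scale.** If average MAP had the SD of 20 mmHg that the protocol assumes for lowest MAP (an assumption here), the standard error of the difference would be 20 × √(2 / 85) = 3.1 mmHg. Even the five-patient excess is below one standard error.

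**The case against.** The strongest reply is that this is detail for an analysis plan. The article mentions such a plan and refers outcome presentation to a supplementary table; neither is shown, and either could hold a rule. That limits how firmly the point can be put. But the article is not simply silent. It fixes no imputation for all outcomes and writes its arrest rule into the primary-outcome paragraph. Following what is written gives the inconsistent scoring.

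Second, a reader might infer that the protocol forbids 10 mmHg for other outcomes. It does not. The sentence speaks of a MAP value in general terms, and the restriction comes only from where it stands. Nor can the no-imputation sentence alone forbid it, because that sentence also covers the primary outcome, which does receive the value. The plan evidently treats 10 mmHg as a scoring rule. What remains is that no such rule is attached to average MAP, so nothing fills the readings after a death.

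Third, a reader might infer that every arrested patient is scored on pre-arrest readings alone. That is exact only for a fatal arrest without return of circulation and with no pressure recorded during the arrest. Resuscitated patients add later readings, invasive monitoring may capture arrest pressures, and a patient who arrests before the first reading has no average at all. Pre-arrest readings may also be low in themselves.

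Fourth, the severe-hypotension gap arises only if no systolic value below 80 mmHg was ever recorded. In a patient deteriorating as in example A, one probably would have been.

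Finally, pressure while alive, reported beside mortality, is a legitimate alternative estimand, and first-hour arrest and death are reported separately, so an imbalance would be visible. This argues for showing both versions, not for leaving the choice open until the data are seen in an open-label trial.

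**Conclusion.** The point holds in limited form. On the text shown, the arrest value and its sensitivity analysis belong by placement to the primary outcome. A fatal first-hour arrest without return of circulation would therefore enter average MAP through pre-arrest readings only, biasing that outcome upwards in the arm with more early deaths.

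The shift is about 0.4 mmHg in the arm mean per such patient among 85, and about 2 mmHg for an excess of five. These figures rest on assumed readings, arrest times and event counts, because the protocol gives no arrest or death rate; they also assume a simple mean, since the article does not say how the average is formed. A reader might infer a large distortion or a threat to the main result. Neither is supported: the effect stays modest unless early deaths are several and unequal, and the primary outcome and sample size are unaffected. It should be settled before analysis because the change is small and the direction of the bias runs against detecting harm.

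**What to change.** Before analysis, add to the analysis text:

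1. For first-hour average MAP, the plan's own arrest value is entered at each scheduled reading at which the patient is in arrest or has died within the hour. If this was always the intention, one sentence saying so is enough.
2. A sensitivity analysis of average MAP uses available (before-arrest) readings only, and both results are reported beside first-hour cardiac arrest and mortality.
3. Arrest or death within the hour without a recordable pressure counts as severe hypotension.
4. The times of arrest and death are recorded. Data collection says that these events are documented within the hour but does not expressly capture when they occur, and item 1 needs the times.

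The cost is a few sentences and, if not already on the form, two time fields. The statistical downside is that a few extreme values widen the SD of average MAP. The sensitivity analysis in item 2 shows how far the result depends on them; it has to be added for this outcome, because the existing before-arrest analysis is written for the primary outcome.
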